#### Sample size {14}

This is a phase II trial to demonstrate some efficacy signal on the primary outcome. The sample size estimation has therefore been estimated based on the “probability of benefit” approach using the Mann-Whitney *U* test with the R Software [32].

Two studies [33, 34] have defined the minimum clinically significant difference between consecutive ratings of pain to be 13 mm in emergency department patients. Assuming that a difference of 13 mm between the groups in the change in pain score from baseline is clinically important (standard deviation of 20 mm—the maximum reported deviation of VAS pain at 30 min in a Cochrane Review [3], then at 5% significance level with 90% power, 53 patients with confirmed renal colic should be recruited per arm.

The standard deviation of the primary outcome in this trial will be used to inform power calculations for the subsequent definitive trial.

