### Outcomes {12}

#### Primary endpoint/outcome

The primary outcome will be the difference in the change in pain scores (measured on a 100-mm visual analogue scale [VAS]) from baseline to 30 min post-drug administration between trial arms in patients with “confirmed renal colic”.

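### The 90% power rests on an SD described as that of the 30-minute VAS score, but the primary test is on change from baseline, and nothing stated links the two

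*Protocol article*

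**What the plan says.** Under 'Primary endpoint/outcome' the protocol article states: "The primary outcome will be the difference in the change in pain scores", measured on a 100-mm VAS from baseline to 30 minutes in confirmed renal colic. 'Primary outcome analysis' compares that change between arms by the Mann-Whitney U test. An ANCOVA of the 30-minute score with baseline as covariate follows as a further analysis.

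'Sample size {14}' sets the target on the same scale: "Assuming that a difference of 13 mm between the groups in the change in pain score from baseline is clinically important", the difference being 13 mm. The variability is given as an SD of 20 mm, described as "the maximum reported deviation of VAS pain at 30 min in a Cochrane Review". The result is: "at 5% significance level with 90% power, 53 patients with confirmed renal colic should be recruited per arm". The section names the Mann-Whitney test as the basis of the calculation.

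No baseline SD, correlation between baseline and 30-minute scores, or SD of change is given. The section ends: "The standard deviation of the primary outcome in this trial will be used to inform power calculations for the subsequent definitive trial".

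**The concern.** The target difference and the test are on the change scale, while the SD, as described, is that of a score at a single time. These are different quantities. The SD of a change depends on both single-time SDs and on the correlation between them, so it can be larger or smaller than the 30-minute SD.

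This calculation is the only justification given for the sample size. A null result would be read against the stated 90%, and if the SD of change exceeds 20 mm the trial would have had less power than that. The same parameter is meant to feed phase III planning, so a confusion between the two SDs could carry forward.

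**Working it through.** **Inputs from the article:** difference 13 mm; SD 20 mm; 5% significance; 90% power; 53 per arm; Mann-Whitney on change. Sidedness is not stated; two-sided is used because it reproduces the stated number.

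**Assumed, because the article gives no figure:** baseline SD (SDb) of 10, 15, 20 or 25 mm; correlation r between 0 and 0.6; normally distributed changes that differ by a shift.

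**Step 1, reproduce the stated figure.** The standardised difference is 13/20 = 0.65. A two-sided t-test needs 50.7 per arm for 90% power. Dividing by the Mann-Whitney efficiency of 3/π gives 50.7 × π/3 = 53.1. Direct Mann-Whitney power, with probability of benefit Φ(0.65/√2) = 0.677, is 89.5% at 52 per arm and 90.1% at 53. The stated 53 is therefore correct for an SD of 20 mm, with almost nothing to spare.

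**Step 2, put the SD on the scale of the endpoint.** If 20 mm is the SD of the 30-minute score,

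SD of change = √(SDb² + 20² − 2 × r × SDb × 20).

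Setting this equal to 20 gives SDb² = 40 × r × SDb, so r = SDb/40. The break-even correlation is 0.625 at SDb 25, 0.5 at 20, 0.375 at 15 and 0.25 at 10. Below it, power is under 90%; above it, power is over 90%.

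**Step 3, Mann-Whitney power at 53 per arm for a 13 mm difference.** The normal-shift formula and simulation agree within about one percentage point.

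| Baseline SD (assumed) | r (assumed) | SD of change | Power |
|---|---|---|---|
| 20 | 0 | 28.3 | about 63% |
| 20 | 0.3 | 23.7 | about 78% |
| 20 | 0.5 | 20.0 | about 90% |
| 20 | 0.6 | 17.9 | about 95% |
| 15 | 0 | 25.0 | about 73% |
| 15 | 0.3 | 21.1 | about 86% |
| 15 | 0.5 | 18.0 | about 95% |
| 10 | 0 | 22.4 | about 82% |
| 10 | 0.3 | 19.5 | about 92% |
| 25 | 0.3 | 26.9 | about 67% |

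Worked example, SDb 20 and r 0.3: √(400 + 400 − 240) = √560 = 23.7 mm; 13/23.7 = 0.55; power about 78%.

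**Step 4, the planned ANCOVA.** For the 30-minute score adjusted for baseline, the residual SD is 20 × √(1 − r²), which never exceeds 20 mm. Power at 53 per arm is about 91% at r = 0, 94% at r = 0.3 and 97% at r = 0.5. An SD of the 30-minute score is on the right scale for this analysis, and no baseline SD is needed.

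**The case against.** Five points can be made for the plan.

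- **The 20 mm may be an SD of change.** The parenthesis comes directly after the mention of change from baseline, so the description of the source may be loose shorthand. The cited review is not available here, so this cannot be excluded. It stands as a reason to ask for clarification, but the text as written says otherwise.
- **The value was chosen as a maximum.** That is a cautious choice and deserves credit. But the largest SD of a 30-minute score does not bound the SD of a change, which reaches 28.3 mm when both SDs are 20 and r = 0.
- **The low power figures rest on assumed inputs.** This stands in full. A reader might infer from the upper rows of the table that the trial is underpowered, at roughly 62 to 78%. That needs a baseline SD near 20 mm together with a correlation of 0 to 0.3, and the document supports neither.
- **Entry in severe pain does not settle the direction.** A reader might argue that it narrows the baseline range, weakens the correlation and so lowers power. But narrowing also shrinks the baseline SD. With the 30-minute SD held at 20 and an assumed regression slope of 0.3, SD of change = √(400 + SDb² × (1 − 0.6)). Moving SDb from 20 to 15 to 10 lowers r from 0.30 to 0.23 to 0.15, yet power rises from about 78% to 83% to 87%. Nor can a narrow baseline be taken for granted: standard analgesia may precede screening, the inclusion criteria state no minimum VAS, and baseline is scored immediately before the trial drug.
- **Part of the remedy is already planned.** The ANCOVA, the confidence intervals and the reporting of the observed SD are all in the protocol. This limits the harm, but the test named first for the primary outcome, and used for the sample size, remains Mann-Whitney on change.

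**Conclusion.** The point holds as an unsupported input, not as an arithmetic error or a demonstrated shortfall. The figure of 53 per arm follows correctly from an SD of 20 mm. What is missing is a reason to take 20 mm as the SD of the change, since the article describes it as the SD of the 30-minute score and gives no baseline SD or correlation to connect the two.

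The stated 90% for the primary test therefore depends on the correlation being at least SDb/40. Over the assumed grid, power runs from about 63% to about 95%, with 90% falling inside that range. These figures assume normal shifts, a two-sided 5% test and a 30-minute SD of exactly 20 mm.

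**What to change.** Any one of these would resolve it:

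1. If the cited source supports it, state in the sample-size section that 20 mm is an SD of change from baseline. The calculation then stands as it is.
2. Keep Mann-Whitney on change and give its power at 53 per arm over a range of SDs of change, for example 18 to 28 mm: about 95% at 18, 90% at 20, 84% at 22, 77% at 24, 70% at 26 and 63% at 28. Use the pooled, blinded SD of change and the baseline/30-minute correlation in participants already recruited to show where the trial lies.
3. Make the already planned baseline-adjusted ANCOVA of the 30-minute VAS the primary test, by amendment before unblinding. With an SD of 20 mm for that score, 53 per arm gives at least about 91% power at any correlation.

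Whichever is chosen, report both the SD of change and the correlation, so that phase III planning uses the right quantity.

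Cost: option 1 is a clarification. Option 2 needs a blinded calculation and revised wording, and the stated power may become less favourable. Option 3 replaces the prespecified primary test in a recruiting trial, so it needs a formal protocol and SAP amendment. None requires more patients.

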#### Recruitment {15}

Approximately 34 patients with a confirmed diagnosis of renal colic were discharged from the Royal Derby Hospital Emergency Department per month prior to the start of the trial. We estimate a recruitment rate of between 18 and 30% of eligible patients. This figure is derived from the current department recruitment to a comparable CTIMP (ISRCTN 34153772), another trial in an ED setting [35], and a discussion with the PPI group.

Following 11 months of study recruitment, the average number of participants with confirmed renal colic recruited in the study per month was 4. In addition, the observed proportion of participants who subsequently were found not to have a renal calculus was 30% instead of 10% that was assumed at the start of the study.

Therefore, we estimate that 106 patients with confirmed renal colic could be recruited in 31 months. This allowed for a slow start in recruitment (3 months to reach 20% recruitment rate) and recruitment plateau during the last 7 months (2 patients with confirmed renal colic recruited per month). This requires the recruitment of approximately 152 patients with suspected renal colic given that approximately 30% of patients with suspected renal colic are subsequently found not to have a renal calculus (local audit data, previous research, and first 6 months of recruitment) [36].

### Assignment of interventions: allocation

#### Sequence generation {16a}

Randomisation will be based on a computer-generated randomisation list, created using random permuted blocks of randomly varying size and implemented using a “scratch card” randomisation system. The randomisation list will be prepared using the NQuery Advisor software by an unblinded statistician. Allocation will be in the ratio of 1:1 without any stratification factors.

#### Concealment mechanism {16b}

Randomisation will be carried out using scratch cards with the allocation concealed by silver scratch-off stickers. The scratch cards will be filed in a card dispenser (or “card shoe”) to allow an unblinded staff member to draw the next card in the correct randomisation order and reduce the chance of re-ordering. The allocation is revealed by scratching off the silver area on the scratch card.

#### Implementation {16c}

An unblinded statistician will generate the randomisation list and prepare the scratch cards in order, using silver scratch-off stickers for concealing the allocation. The cards will be filed in the card dispenser and an unblinded staff member (not involved in the patient’s treatment and data collection) will draw the next card, scratch off the silver area and reveal the patient’s allocation. Patients will be enrolled and eligibility confirmed by a member of the research team before randomisation occurs.

### Assignment of interventions: blinding

#### Who will be blinded {17a}

In order to maintain the blind for treatment administration, both trial treatments will be presented as identical syringes containing 5 ml of a colourless solution labelled with a pre-printed trial label. This will be prepared by unblinded staff delegated responsibility for randomising patients and preparing the trial medication. No staff member with knowledge of the treatment allocation, will have any involvement in collecting trial data or administering trial treatment.

The SARC trial manager will be blinded to the allocation, and any monitoring that would result in unblinding of allocation will be performed by an unblended sponsor representative. Preparation of unblinded DMEC reports will be completed by a designated unblinded statistician not involved in the design and analysis of the trial.

#### Procedure for unblinding if needed {17b}

Unblinding of participants should only occur for valid medical or safety reasons, e.g. in the case of a severe adverse event where it is necessary to know which treatment the patient is receiving before they can be treated. All instances of unplanned patient unblinding should be clearly documented in the participant’s medical notes (together with the reasons for doing so) and recorded in the investigator site file. Details regarding the unblinding of participants must be forwarded to the chief investigator and the sponsor (via the Derby CTSU Trial Manager) without revealing the allocation.

The responsibility for the emergency unblinding of any participant on the trial resides with the investigator. If emergency unblinding is required for clinical reasons, this can be initiated by any treating healthcare professional. They will not be required to discuss unblinding with anyone in the research team if they feel that unblinding is necessary. The sponsor is not required to be involved in the decision to unblind a patient in an emergency situation.

The randomisation list for the trial must be held securely within the pharmacy department, in a controlled area, separate from the investigator site file and easily accessible by those authorised to reveal treatment allocation at the site.

### Data collection and management

#### Plans for assessment and collection of outcomes {18a}

Assessments will be undertaken by the staff blinded to the treatment allocation at the specified time points until either 24 h after administration of trial medication or discharge from the hospital (whichever is sooner).

All pain score measurements for the trial will use a visual analogue scale [VAS] 0–100 mm (apart from the pre-enrolment score to ensure eligibility, which will be a NAS as per routine practice). The visual analogue scale will be a 100-mm line with cues at either end (0 = no pain, 100 mm = worst pain), and participants will be asked to mark their current pain score with a cross at each time point listed below. The qualitative assessment of participants’ pain will be obtained using the short-form McGill Pain Questionnaire.

Participants will be asked to complete a satisfaction questionnaire regarding pain relief and their experience of the trial in the emergency department. The presence/absence of renal calculus will be determined by appropriate imaging (CT renal tract or XR KUB); this takes place during normal treatment and within 24 h of admission in routine practice. The research team will record trial-specific observations directly onto the eCRF.

Information about AKI development within 7 days from admission will be collected from the patient’s notes retrospectively.

#### Plans to promote participant retention and complete follow-up {18b}

Participant dropout/loss to follow-up is not expected to present an issue due to the short duration of patient involvement; however, it is recognised that the frequency of assessments may result in a higher incidence of missing data. Participants will be actively monitored for safety reasons until 120 min post-treatment administration and therefore the research staff should be able to ensure the completion of outcome data. Should the participant be transferred to a different department, they will be provided with a booklet containing the VAS pain score outcomes and asked to complete these. A timer will be provided to serve as a reminder for when assessments are needed.

### Data management {19}

#### Data collection tools and source document identification

An electronic software platform will be used for trial data capture. Data capture will be via a web-based, fully validated system, compliant with 21 CRF Part 11; Electronic records; Electronic signatures and EU Commission Directive 2005/28/EC with comprehensive audit trials. DCTSU will be responsible for database build and system validation. Data will be hosted externally according to General Data Protection Regulation guidance.

#### Source data

Source data will consist of paper and electronic medical records depending on the data being collected. Patient-reported outcomes (specifically the McGill Questionnaire, Patient Satisfaction and VAS) will be recorded directly onto paper which will serve as the source data prior to being transcribed onto the eCRF. There may be some instances where the data is transcribed directly onto the eCRF, and this will be determined with the PI prior to the start of the trial at the site.

#### Data handling and record keeping

The investigator and trial team will ensure that the participant’s identity is protected at every stage of their participation within the trial, according to the Caldicott principles. If any patient information needs to be sent to a third party, the trial team will adhere to maintaining pseudo-anonymous participant parameters in correspondence.

The trial database will be designed to capture the clinical data in accordance with the best principles of clinical data management and the relevant SOPs on Clinical Data Management System Specification and Validation, Data Capture, Instrument Design and Database Development developed by the Derby CTSU.

Access to the trial database will be restricted by role-based permission to authorised trial personnel. Users will be suitably trained on the system prior to being granted access. Individual user accounts will be password-protected and will not be shared between members of the trial team.

Data will be entered into the eCRF using worksheets and source documents at the site. Post-data entry, validation checks will be performed on the data to ensure accuracy and consistency according to the data validation plan. All data queries generated as a result of these checks will be available for resolution by the site online. After data entry is complete, all data queries have been resolved and medical coding is completed, the database will be locked and released for statistical analysis.

All clinical data will be collected, stored, processed and archived in accordance with the Data Management Plan for this trial and in line with the relevant SOPs on data entry, data quality assessment, data validation, database lock and data transfer and archiving developed by the Derby CTSU and any relevant legislation.

Access will be granted to authorised representatives from the sponsor, trial team and the regulatory authorities to permit trial-related monitoring, audits and inspections. The purpose of these inspections is to verify and corroborate the data collected on the case report forms. In order to do this direct access to medical or clinic records is necessary. The CI/PI must inform the sponsor if they are notified of a forthcoming audit by the IEC/IRB or regulatory authorities.

The principal investigator will ensure that the following information is contained in the medical or clinic records of the participant and that the entries are signed and dated:
Sufficient data to allow verification of the entry criteria in terms of past and present medical and medication histories.The day the participant entered the trial describing the trial number, the treatment being evaluated, the unique number assigned to the participant and a statement that informed consent was obtained.Each subsequent trial visit including any concerns about adverse events and their resolution.Any deviation from the protocol procedures and subsequent impact on endpoint data validity.All concomitant medication taken by the participant, including start and stop dates.The date when the participant finished the trial, the reason for termination and the participant’s general condition at trial completion.

#### Access to data

Direct access will be granted to authorised representatives from the sponsor, Derby CTSU, host institution and regulatory authorities to permit trial-related monitoring, audits and inspections.

#### Confidentiality {27}

The trial will be conducted in accordance with the Data Protection Act 2018 and other applicable legislation, including but not limited to the EU General Data Protection Regulation. The investigator must ensure that the participant’s anonymity is maintained throughout the trial and following completion of the trial. Participants will be identified on all trial-specific documents (except for the screening log, informed consent form and enrolment log) only by the participants’ trial-specific identifier. This identifier will be recorded on all trial documents and the database. The investigator site file will hold an identification log detailing the trial-specific identifier alongside the names of all participants enrolled in the trial.

All documents will be stored securely with access restricted to trial staff and authorised personnel.

[name], as the chief investigator, will act as the custodian of the data generated in the trial.

#### Plans for collection, laboratory evaluation and storage of biological specimens for genetic or molecular analysis in this trial/future use {33}

The study does not collect biological specimens for analysis and storage or for use in future research.

## Statistical methods

### Statistical methods for primary and secondary outcomes {20a}

The statistical analysis will be undertaken by the trial statistician. The trial statistician will draft the statistical analysis plan (SAP), which will be reviewed by the Trial Management Group (TMG), the Trial Steering Committee (TSC) and the Data Monitoring and Ethics Committee (DMEC). The finalised SAP will be approved and signed by the CI and the trial statistician.

### Primary outcome analysis

The primary outcome of the change in pain scores (measured with VAS) from baseline to 30 min in patients with “confirmed renal colic” will be compared between the two trial arms using the Mann-Whitney *U* test. Further analysis of the primary endpoint will be carried out using an analysis of covariance (ANCOVA) approach, analysing the pain scores at 30 min and including the baseline pain scores as a covariate, along with any other clinical/demographic covariates of import, e.g. age, gender and weight. The results of the primary endpoint will be reported as the mean change in pain score for each treatment arm along with associated 95% confidence intervals.

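### The one stated form of the primary result is mean change per arm with per-arm confidence intervals, although the outcome and sample size concern a between-arm difference and the test is rank-based

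*Protocol article*

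**What the plan says.** All places are in the protocol article.

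- **Primary endpoint/outcome.** The quantity of interest is a contrast between arms: "The primary outcome will be the difference in the change in pain scores", from baseline to 30 min, in patients with confirmed renal colic.
- **Sample size {14}.** The target is also a contrast: "Assuming that a difference of 13 mm between the groups in the change in pain score from baseline is clinically important", with a "standard deviation of 20 mm". The calculation uses a probability-of-benefit approach with the Mann-Whitney test and gives 53 confirmed cases per arm at a 5% level and 90% power.
- **Primary outcome analysis.** The change scores "will be compared between the two trial arms using the Mann-Whitney" U test. Then: "Further analysis of the primary endpoint will be carried out using an analysis of covariance (ANCOVA) approach, analysing the pain scores at 30 min" with baseline pain and other covariates of importance. The closing sentence fixes the form of the result: it will be "reported as the mean change in pain score for each treatment arm along with associated 95% confidence intervals".

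No section names a mean difference, a Hodges-Lehmann shift, a probability of benefit or an adjusted ANCOVA difference, with its interval, as something to be reported for the primary endpoint.

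**The concern.** Three quantities should line up: what the trial wants to know, what it tests, and what it reports. The first is a difference between arms. The second is a rank comparison between arms. The third, as written, is a pair of within-arm means with within-arm intervals. That pair does not express the contrast, and it is not the parameter that the Mann-Whitney test addresses.

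Within-arm change is also a poor carrier of the treatment effect here. Patients enter with severe pain and both arms receive standard analgesia, so pain is likely to fall in both for reasons unrelated to salbutamol. An interval for one arm's change says little about what the drug adds.

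What is at stake is how the headline result is read. A phase II trial that looks for an efficacy signal and guides a phase III trial needs an interval that can be set against 0 and 13 mm. Neither per-arm interval can be used in that way.

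This is a reporting rule that the article states, not a detail left to the SAP. A SAP that follows the sentence inherits the mismatch, and one that departs from it disagrees with the protocol.

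**Working it through.** **Inputs.** From Sample size {14}: difference 13 mm, SD 20 mm (used by the plan as the SD of the change), 5% level, 90% power, 53 per arm. From Trial design {8}: 1:1 allocation. Assumed, because not stated: two-sided test, normal data, equal SDs.

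**1. The plan's own figure.**
- Normal-approximation n per arm = 2 × [20 × (1.960 + 1.282) / 13]² = 49.7.
- Divided by the Mann-Whitney efficiency 3/π = 0.955, this gives 52.1, rounded up to 53.
- Simulated two-sided Mann-Whitney power at 53 per arm is 0.896.

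So 53 per arm reproduces as a two-sided Mann-Whitney size. The sample size is not in question.

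**2. Interval that the plan says it will report, per arm.**
- Half-width = t(52) × SD/√n = 2.007 × 20/√53 = 5.5 mm.
- Two such intervals stop overlapping only when the means differ by more than 2 × 5.51 = 11.0 mm.

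**3. Interval that answers the question.**
- Standard error of the difference = 20 × √(2/53) = 3.885 mm.
- Half-width = t(104) × 3.885 = 1.983 × 3.885 = 7.7 mm.
- The Hodges-Lehmann interval, which matches the Mann-Whitney test, has an average half-width of about 7.9 mm by simulation.

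**4. The two displays compared.**
- A difference above 7.7 mm is significant at 5% on a t-test.
- A difference of 11.0 mm, where the per-arm intervals just separate, gives 11.03/3.885 = 2.84, or p of about 0.005.
- Observed differences between 7.7 and 11.0 mm therefore show overlapping per-arm intervals although p < 0.05.
- The ratio 11.0/7.7 = 1.43 does not depend on the SD, since both half-widths are proportional to it.

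**5. How often this would arise.** If the true difference is 13 mm, P(7.7 < d < 11.0) = Φ((11.0 − 13)/3.885) − Φ((7.7 − 13)/3.885) = Φ(−0.51) − Φ(−1.36), about 0.22.

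**6. The target on the scale used for sizing.** Under the planning assumptions, 13 mm corresponds to a probability of benefit of Φ(13/(20√2)) = Φ(0.46) = 0.68, against 0.50 for no effect.

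**The case against.** The best defence is that little or nothing is lost, and much of it stands.

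- **The ANCOVA.** A reader might infer that the plan yields no estimate of the treatment effect. That is not so. The ANCOVA in the same section gives a baseline-adjusted between-arm difference, and with baseline as a covariate its treatment coefficient is the same for the 30-min score as for the change. What remains is that it is labelled further analysis, its covariates are only exemplified, and its coefficient is not said to be reported.
- **Reconstruction.** A reader might infer that a 13 mm benefit could be neither supported nor ruled out. The arms are independent, so the difference is a subtraction and its half-width is about √(5.5² + 5.5²) = 7.8 mm, close to 7.7. The information survives, but the reader has to rebuild it.
- **Within-arm intervals and zero.** It is tempting to say that each arm's interval must exclude zero whatever the drug does. The article gives no expected placebo change. Standard analgesia may be given before screening, and baseline is taken immediately before the trial drug, so part of its effect may already be in the baseline score. A fall in both arms is likely but not established.
- **The 22%.** This is not an error rate of the trial. Inference rests on the between-arm Mann-Whitney test, and nothing makes interval overlap a decision rule. The figure says how often the display could mislead.
- **Scope.** The sentence does not say that only per-arm means will be given. Per-arm summaries have a purpose too: the mean and SD of the primary outcome are a listed secondary outcome, and the SD is to inform the next trial. The SAP, which is not shown, may already name an effect measure, so its absence from the article is not itself a fault.

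None of this makes the sentence that was written match the outcome it reports.

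**Conclusion.** The point holds as a mismatch in a stated reporting rule. The outcome and the 13 mm target are between-arm, the test is rank-based, and the only reporting form given is per-arm means with per-arm intervals. No between-arm estimate with an interval is named as the primary result or tied to the primary test.

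The effect is on reading, not on validity. Over observed differences of 7.7 to 11.0 mm, the planned display can look inconclusive although the comparison is significant. This rests on an SD of 20 mm in both arms, 53 per arm, normal data, a two-sided 5% level and a t-test as stand-in for Mann-Whitney. The type I error rate, the power and the choice of primary test are not affected.

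A reader might also conclude that the ANCOVA should become the primary analysis. The documents do not require that. It would change the primary test that the sample size was built on, which goes beyond correcting the reporting sentence.

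**What to change.** Amend the closing sentence of Primary outcome analysis, and carry the same wording into the SAP, so that:

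- the primary result is the between-arm difference in change from baseline to 30 min with its 95% interval, given as the Hodges-Lehmann shift and/or the probability of benefit, alongside the Mann-Whitney p-value;
- the baseline-adjusted ANCOVA difference with its 95% interval is the supporting estimate;
- differences in mm are read against 0 and 13 mm;
- per-arm means and SDs are kept as description.

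The cost is one sentence of protocol and SAP wording. The primary test, the 53 per arm, data collection and trial conduct do not change.
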